#### Data analysis

We will conduct linear mixed models to investigate significant changes over time for both primary and secondary outcomes following the intention to treat principle, i.e., all available data will be analyzed according to the group they are randomly assigned. The use of LMM also provides the means to include subjects with incomplete and use all available data to assess the treatment effect over time. In this model, intervention group, time, and the interactions between the intervention groups and time will serve as predictors with duration of knee pain and number of comorbidities as covariates. Given the longitudinal nature of the clinical trial data, we assume the autoregressive covariance structure will be the best fit for the data, but the statistical fitness by using other covariance structures will also be evaluated [52].

With a clearly defined target population, effectiveness and safety outcomes, and convenient data collection procedures, our trial should realize the goal of maximizing the number of participants who are maintained on the protocol-specified intervention until the outcome data are collected. In case of a large number of outcomes and covariates with missing data, we will use multivariate imputation using chained equations (MICE) to incorporate auxiliary information about the missing data. The imputation model will include prerequisite variables in the data analysis, variables for baseline socio-economic status, and also variables that are predictors of outcomes. About 10 iterations will be conducted in each imputation process with more iterations to be considered until the chain reaches convergence [53]. Twenty completed datasets will be imputed with the use of the chain equations. The Rubin’s rule will be applied to combine the effect estimates [54]. This approach provides estimated standard errors and *P* values that incorporate missing-data uncertainty. For the patients that meet any of the exclusion criteria such as alternative treatment or severe outcome, then all subsequent longitudinal measurements since that date of the event will be excluded from the analysis.

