**Method:**

Seventy-six participants with KOA will be recruited from the community. We will conduct a single center, parallel group, superiority randomized controlled trial comparing DPT and NS injections, with blinding of physician, participants, outcome assessors and statisticians. Each group will receive injections at week 0, 4, 8 and 16. The primary outcome will be the Western Ontario McMaster University Osteoarthritis Index pain scale (WOMAC), and secondary outcomes include WOMAC composite score, the WOMAC function and stiffness subscale, the Visual Analogue Score of pain, objective physical function tests (the 30 s chair stand, 40- m fast paced walk test, the Timed up and go test) and the EuroQol-5D (EQ-5D). All outcomes will be evaluated at baseline, and 16, 26 and 52 weeks. All analyses will be conducted on an intention-to-treat basis using linear mixed regression models.

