### Randomization and Allocation Concealment

Blocked randomization in 1:1 ratio will be used to allocate patients to the two groups [41]. The sequence will be generated by the Random Allocation Software. Random sequence will be concealed using sequentially numbered, opaque sealed envelopes (SNOSE) procedure [42]. These SNOSE will be kept by a person not involved in the care or evaluation of patients, or in the data analysis. The investigator enrolling the patient will have no access to SNOSE. The treatment allocation process starts when the investigator calls the personnel keeping the SNOSE. The computer database is designed in such a way that treatment allocation cannot be changed after randomization. Each participant will receive the SNOSE and they will be asked to sign on it. The SNOSE will only be opened at 52-week.

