#### Secondary outcomes

Secondary outcomes include WOMAC composite score, the WOMAC function and stiffness score. Objective physical function is measured using the 30-s chair stand performance test, 40 m fast-paced walk test and the timed up –and-go test (TUGT). The three tests are recommended by the Osteoarthritis Research Society International (OARSI) as performance-based tests to assess physical function in people diagnosed with KOA [50]. Health related quality of life is assessed using the EuroQuol-5 questionnaire. The measure has strong construct validity, responsiveness and clinometric profile; it has been used to assess the economic impact of OA [35]. Joint pain will also be assessed by the Visual Analogue Score (VAS) in 0–100 mm scale upon walking in the past 48 h. Analgesic consumption will be assessed by the number of participants on analgesics by the 7-day recall diary. Before un-blinding, treatment satisfaction will be tested by asking “Would you recommend the therapy to others with knee OA like yours?”

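### Linear mixed models are prescribed for every secondary outcome, but analgesic use is binary and the recommend question is apparently asked only once, so the stated model does not fit either

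*Protocol article*

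**What the plan says.** The Data analysis section of the protocol article fixes one model family for the whole trial: "We will conduct linear mixed models to investigate significant changes over time for both primary and secondary outcomes". It then gives the fixed effects: "In this model, intervention group, time, and the interactions between the intervention groups and time will serve as predictors", with two baseline covariates. On the within-person correlation it says "we assume the autoregressive covariance structure will be the best fit for the data", and adds that other structures will be compared for fit. The abstract is broader still: "All analyses will be conducted on an intention-to-treat basis using linear mixed regression models".

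The Secondary outcomes section includes two items of a different kind:

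- Analgesic use: "Analgesic consumption will be assessed by the number of participants on analgesics by the 7-day recall diary".
- Treatment satisfaction: "Before un-blinding, treatment satisfaction will be tested by asking", followed by the item "Would you recommend the therapy to others with knee OA like yours". No response scale is printed.

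On the time of un-blinding, the section on randomization and allocation concealment says "The SNOSE will only be opened at 52-week". The Data collection and management section sets assessments at baseline and weeks 16, 26 and 52, and the abstract says that every outcome is evaluated at those four times. The article names no logistic model, GEE or comparison of proportions for any outcome.

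**The concern.** A linear mixed model with a group-by-time term assumes a roughly continuous response measured repeatedly in each person. Each of the two outcomes breaks a different part of that.

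For a yes/no variable the variance is p(1 − p), so it changes whenever the proportion changes between visits. A model with one common variance can then give standard errors that are too small for one contrast and too large for another. For a question asked at a single time there is no change over time to model.

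Analgesic use is useful context for the pain result, because the Interventions section allows usual analgesics from 48 hours after injection and allows co-interventions in both groups. For satisfaction, the prescribed analysis has to be replaced in any case. If the replacement is chosen after the data are seen, it is an unplanned departure, open to selection among methods.

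**Working it through.** The plan gives no figure on this point, so there is none to reproduce. The check has three parts.

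**1. Outcome type and timing against the stated model**

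| Secondary outcome | Type per participant | Times | Fits the stated model? |
|---|---|---|---|
| WOMAC scores, VAS, performance tests, EQ-5D | treated as continuous | 4 | yes |
| Analgesic use | on analgesics or not | 4, by the general schedule | can be fitted, but misspecified |
| Recommend question | yes/no inferred from wording | 1, inferred from un-blinding at week 52 | no |

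**2. Recommend question: can the terms be estimated?**

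The fixed-effects columns are 1, g, t and g·t. With one assessment time, t equals a constant c for everyone, so t = c·1 and g·t = c·g. Only two of the four columns are independent (rank 2 of 4). Time and group-by-time are not estimable. With one observation per person, an autoregressive or any other within-person correlation cannot be identified either. A graded response scale would not change this. Nor does the abstract's four-visit schedule, because at baseline there is no treatment experience to recommend.

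**3. Analgesic use: how wrong can the error bars be?**

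The article gives no proportions, so everything here is assumed. Take use of 90%, 70%, 60% and 50% at the four visits in both arms.

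- Variances p(1 − p): 0.09, 0.21, 0.24, 0.25. Mean = 0.79/4 = 0.1975.
- Raw week-52 difference under one common variance: SE ratio = √(0.1975/0.25) = 0.889, about 11% too small. Actual level of the nominal 5% test: 2Φ(−1.96 × 0.889) ≈ 8%.
- Group difference in change from baseline to week 52, same proportions, zero within-person correlation: the true variance of change is 0.09 + 0.25 = 0.34, while the model uses 2 × 0.1975 = 0.395. SE ratio = √(0.395/0.34) = 1.078, too large. Actual level: 2Φ(−1.96 × 1.078) ≈ 3.5%.

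The same data therefore give a liberal test for one contrast and a conservative test for the other. Simulation with no treatment effect and 38 per arm (76/2) gives the range:

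| Assumed use | Contrast | Trials | Rejected at nominal 5% |
|---|---|---|---|
| 70% to 40% | group-by-time, week 52 | 300 | 5.3% |
| 70% to 10% | group-by-time, week 52 | 300 | 4.3% |
| 95% to 5% | group-by-time, week 52 | 300 | 1.3% |
| 90/70/60/50% | raw week-52 difference, latent correlation 0 to 0.7 | 20,000 | 8.1% to 8.5% |
| 90/70/60/50% | baseline-to-week-52 interaction, same runs | 20,000 | 3.5% to 5.9% |
| 90/70/60/50% | raw week-52 difference, random intercept | 500 each | 7% to 9% |
| 90/70/60/50% | group-by-time, random intercept, latent correlation 0.3 / 0.6 / 0.8 | 500 each | 4.6% / 5.8% / 7.8% |

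In the first three rows, fitted probabilities fell outside 0 to 1 in 9%, 59% and 91% of trials. The simulation error (one SE at 5%) is √(0.05 × 0.95/300) = 1.3 points for 300 trials and √(0.05 × 0.95/500) = 1.0 point for 500. The 5.3%, 4.3%, 4.6% and 5.8% are therefore compatible with 5%, while the 1.3% and 7.8% are not. All rows use a model with one common variance, by random intercept or compound symmetry.

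**The case against.** The strongest reply is that the model sentence is about changes over time in longitudinal data, so it never meant to cover an item asked once. The abstract's list of secondary outcomes and the secondary aims in the Background both leave out analgesic use and satisfaction. On that reading the article does not describe the analysis of two small items, which a condensed article may do. This could cover the recommend question. It does not cover analgesic use, which sits under Secondary outcomes, follows the general visit schedule, and has no other method anywhere. The plan assigns it a method, so this is not a matter of something left to a fuller document.

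A second reply is that a linear model on a 0/1 outcome is a linear probability model whose group contrasts are risk differences, and that its test is often close to nominal. That stands: for analgesic use the model is misspecified but not useless, and a reader who infers that it is invalid or cannot be fitted goes too far.

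A third reply is that the plan will compare other covariance structures, and one with a separate variance per visit removes most of the problem with the standard errors. That also stands. It depends, however, on that structure being chosen, and it does not keep fitted probabilities between 0 and 1.

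Finally, the yes/no format and the single week-52 timing of the recommend question are inferred, since the article prints no response scale.

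**Conclusion.** The point holds as a minor one, confined to two secondary outcomes.

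- **Recommend question:** if it is asked once, as the un-blinding rule implies, the stated model cannot be estimated. An analyst would see this at once, so the practical risk is an unplanned choice of replacement, not a wrong published result.
- **Analgesic use:** the stated model runs but is misspecified. Under the assumed proportions and a common variance, the nominal 5% test ran from about 1% to 8–9%, in either direction.

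Two stronger readings are not supported. A reader might take 8% as the general false-positive rate. It belongs to the raw week-52 contrast under one assumed set of proportions and a common variance; the group-by-time test, whose terms the plan names, ran from about 1% to 8%. A reader might also infer that the primary result is undermined. The WOMAC pain analysis is not affected by how these two variables are modelled, and neither is a covariate in its model.

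**What to change.** In the Data analysis section:

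- Restrict linear mixed models to the continuous, repeatedly measured outcomes.
- For analgesic use, specify a logistic GEE or logistic mixed model with visit and group-by-visit, and report the week-52 risk difference with a 95% CI.
- For the recommend question, state the response scale and the single assessment time. Compare the groups once before un-blinding, as a difference in proportions with an exact or score interval, or with an ordinal comparison if the scale is graded.

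In the abstract, limit the statement that all analyses use linear mixed models, and the statement that all outcomes are measured at four times including baseline, to the outcomes for which they are true.

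The cost is a few sentences and standard code. No new data are needed, and the sample size and the primary analysis do not change.

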### Statistical issues

#### Sample size Calculation

The sample size calculation is based on 2 RCTs which evaluated the intra-articular injection of DPT and NS for KOA at 6 months [32, 51], assuming their therapeutic effect will remain stable for 1 year. The baseline characteristics of the two trials had comparable age, sex, BMI, and baseline WOMAC score. The mean (Standard Deviation) difference of WOMAC scores at 6 month compared with baseline status was 25.2 (20.3) points for DPT [32], and 9.53 (26.6) points for NS [51], respectively. Thus, assuming a pooled SD of 26.6, a sample size of 34 participants in each arm will have 80% power to detect a significant effect size of 0.70 in a two-sample t-test with alpha set at 0.05. Assuming 10% dropout rate, the total sample size is 76.

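### The stated mixed model neither adjusts for baseline WOMAC nor gives the arms a common baseline mean, so its week-52 contrast is unbiased but less precise than it need be

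*Protocol article*

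**What the plan says.** The Data analysis section names the predictors as intervention group, time and their interaction, and then closes the list: "interactions between the intervention groups and time will serve as predictors with duration of knee pain and number of comorbidities as covariates". It says the models are meant to examine change over time, for primary and secondary outcomes alike. It mentions neither a baseline covariate nor equal baseline means.

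Baseline values will exist for every outcome. The Abstract says "All outcomes will be evaluated at baseline, and 16, 26 and 52 weeks", and the Data collection section gives the same schedule. The primary aim, in the Background, is knee pain at 52 weeks.

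The Sample size section also works in changes. Its inputs are described as "The mean (Standard Deviation) difference of WOMAC scores at 6 month compared with baseline status". The values are a mean of 25.2 with SD 20.3 in the DPT trial, and a mean of 9.53 with SD 26.6 in the saline trial. Taking the larger SD as the pooled one, the section states that "a sample size of 34 participants in each arm will have 80% power". It puts the standardized effect behind this at 0.70 and names an unpaired t-test at the 5% level.

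**The concern.** Baseline WOMAC pain is measured in everyone and should be a useful predictor of WOMAC pain a year later. The stated model spends its covariates on pain duration and comorbidity count and does not use baseline WOMAC in the most efficient way.

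There are two readings of how baseline enters. If it is the first repeated response, which fits the aim of studying change, the week-52 interaction term compares raw changes. If baseline is not in the model, the comparison rests on follow-up values alone. Either way the estimate is less precise than a baseline-adjusted one. In a trial of 76 patients, the width of the confidence interval for the primary result is at stake, not its validity.

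**Working it through.** **1. The plan's own sample size.** Inputs: effect size 0.70, 80% power, alpha 0.05 (taken as two-sided), t-test. This gives n = 33.02, so 34 per arm, with power 81.2% at 34. Allowing for 10% dropout, 68/0.9 = 75.6, so 76. The figure reproduces from 0.70.

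**2. The effect size from the plan's inputs.** (25.2 − 9.53)/26.6 = 15.67/26.6 = 0.589, not 0.70. At 34 per arm the power is 67%, and 80% would need 47 per arm. With the root-mean-square of the two SDs, √((20.3² + 26.6²)/2) = 23.66, the effect size is 0.66 and the power 77%. This mismatch is a separate matter. It is used here only to set a starting point.

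**3. Variance of the week-52 contrast.** Let r be the correlation of baseline with week-52 WOMAC. Assume equal variances (set to 1) and complete data, and leave out the common factor 2/n.
- Baseline as response, free group effect, categorical time: Var(Y52 − Y0) = 2(1 − r).
- Baseline as covariate, or common baseline mean: 1 − r².
- Ratio: (1 − r²)/[2(1 − r)] = (1 + r)/2.

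Generalized least squares on four visits confirms this. Compound symmetry with r = 0.7 gives 0.60 against 0.51, ratio 0.85. Autoregressive with 0.8 between adjacent visits (r = 0.512) gives 0.976 against 0.738, ratio 0.756.

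**4. The two listed covariates.** As a time-constant main effect, a covariate adds the same amount to a patient's baseline and week-52 values. It drops out of Y52 − Y0, so it brings essentially no precision to this contrast.

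**5. Size over an assumed range of r.** Extra patients = 1/ratio − 1. The sample-size SDs are SDs of change, so the adjusted effect size is d/√ratio. Power is at 34 per arm, before adjustment 67% (SD 26.6) or 77% (SD 23.66).

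| r (assumed) | Ratio | Extra patients | Power, SD 26.6 | n per arm for 80%, SD 26.6 | Power, SD 23.66 |
|---|---|---|---|---|---|
| 0.3 | 0.65 | 54% | 84% | 31 | 92% |
| 0.5 | 0.75 | 33% | 79% | 35 | 87% |
| 0.7 | 0.85 | 18% | 74% | 40 | 83% |
| 0.8 | 0.90 | 11% | 71% | 42 | 81% |

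With SD 26.6, adjustment reaches 80% power only if r is about 0.45 or less.

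**6. The other reading.** If baseline is not modelled at all, the variance without adjustment is 1 and the ratio is 1 − r²: 0.91, 0.75, 0.51 and 0.36 at r = 0.3, 0.5, 0.7 and 0.8. The table above does not apply to this reading.

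**The case against.** The strongest reply is that nothing here is wrong. A model with group, time and their interaction is standard, is unbiased under randomization, and matches both the aim of studying change and the change-based sample size. How baseline is coded, and whether time is categorical, may be settled in a full protocol or SAP that is not shown. This stands as far as validity goes, so the point is one of efficiency only. It does not remove the point, because the article itself names the model terms and chooses the covariates.

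A reader might also infer more than the text supports:
- **That baseline is discarded.** On the natural reading it is the first response, so it is used, though not optimally. The loss is then (1 − r)/2 of the variance, which shrinks as baseline becomes more predictive.
- **That adjustment rescues the power.** The correlation is unknown, and at r = 0.8 power moves only from 67% to 71%. The inputs are 6-month WOMAC scores with no subscale named, while the primary outcome is WOMAC pain at 52 weeks. Power for the primary outcome cannot be computed from this document.
- **That chance baseline imbalance threatens the result.** With 38 per arm, the SD of a chance baseline difference is √(2/38) = 0.23 SD. A change score already subtracts that difference and over-corrects by (1 − r) times it: about 0.12 SD at r = 0.5 and 0.07 SD at r = 0.7. Averaged over randomizations there is no bias, and the standard error already reflects this variation.

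**Conclusion.** The point holds as a loss of precision in a model that the article itself specifies. On the natural reading, baseline adjustment multiplies the variance of the week-52 contrast by (1 + r)/2, which is 0.65 to 0.90 for r from 0.3 to 0.8. The direction holds for every r below 1. The size depends on an assumed r, and the exact ratio needs categorical time, complete data and equal variances. The rise in power from 67% to between 84% and 71% is an illustration on the plan's own inputs, not a forecast for WOMAC pain. The documents do not support calling the planned analysis biased or invalid. The gap between 0.70 and 0.589 needs its own correction. The change is worth making because the data will be in hand anyway.

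**What to change.** Before unblinding, state how baseline enters the model for WOMAC pain and for each continuous secondary outcome. Choose one of two forms, not both, since using baseline as response and covariate in the same model would count it twice:
- keep baseline as a response and give both arms one common baseline mean, with no group effect at baseline; or
- model weeks 16, 26 and 52 as responses, with the baseline value and its interaction with visit as covariates.

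The two can differ slightly when data are missing, so the choice should be named in advance. If pain duration and number of comorbidities are kept, let each interact with visit so that they can contribute to the week-52 comparison.

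The cost is a sentence or two of model specification and a few degrees of freedom. No new data are needed and no alpha is spent. Fixing the choice before unblinding also prevents it from being made with the results in view.

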### Eligibility

Eligibility will be screened by a trained research assistant using a phone interview, and potential eligible participants will be invited to meet the principal investigator (a physician) at the study site for confirming eligibility based on the following eligibility criteria:

Inclusion criteria include: (1) age ≥ 45 to ≤75 years old; we set the upper age limit to ensure adequate potential for cartilage regeneration [37]; (2) diagnosis of primary knee OA based on clinical and radiological criteria as defined by the American Rheumatology Association [38]; (3) moderate to severe knee pain for at least 3 months, defined as a score of ≥3 (0–6 ordinal response scale) on the question “What is the average level of your left/right knee pain in the past 3 months?”; and (4) failure to achieve pain reduction to a score < 3 (0–6 ordinal response scale) after 6 months of usual care, such as weight reduction, exercise, physical therapy and pharmacological treatment.

Exclusion Criteria include (1) history of corn allergy [39, 40]; (2) previous knee replacement surgery on the referring knee; (3) pregnancy; (4) body mass index (BMI) ≥ 35 kg/m^2^; (5) patients on anti-coagulant therapy; (6) prior knee injections within 3 months; (7) inflammatory or post-infectious knee arthritis, such as clinically diagnosed rheumatoid arthritis, gouty arthritis, psoriatic arthritis and septic arthritis; (8) significant effusion as defined by a ballotable patella; and (9) co-morbidity or lifestyle preventing participation in the study protocol.

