### Baseline measurement

Demographic data such as age, gender and BMI will be collected. Since objective functional outcome will be evaluated in this trial, the baseline physical activity status will be assessed using the Chinese version of International Physical Activity Questionnaire (IPAQ) [44]. Duration of knee pain and prior knee interventions such as weight reduction, knee exercise, physiotherapy, hyaluronic acid injection, corticosteroid injection or Traditional Chinese Medicine (TCM) etc. will be collected. All other co-morbidities will be documented as potential confounders. The severity of KOA will be graded by radiologist using the Kellgren-Lawrence Grading [45].

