### Data collection and management

Data will be collected at baseline, and at week 16, 26 and 52. We will record the number of potential candidates, responses received and their resolution, and the number of injection and assessment sessions attended. Follow up data will include the number at each follow up, the number of participants completing the trial, and the number of withdrawals due to all causes. Data entry, transfer and subsequent maintenance will be performed by a data manager. An electronic database will be used, and the server is in a physically secured location with backup on weekly basis. Access to study data is restricted to the study research team by username and password.

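### Kellgren-Lawrence grade is collected at baseline but left out of the pre-specified covariates; adding it, in the right form, could give a small gain in precision at almost no cost

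*Protocol article*

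**What the plan says.** - **Model (Data analysis).** The analysis is described as follows: "We will conduct linear mixed models to investigate significant changes over time for both primary and secondary outcomes". The model contains the treatment arm, the visit and the arm-by-visit interaction, "with duration of knee pain and number of comorbidities as covariates". No other covariate is named, and no reason is given for choosing these two.
- **Severity (Baseline measurement).** "The severity of KOA will be graded by radiologist using the Kellgren-Lawrence Grading".
- **Allocation (Randomization and Allocation Concealment).** "Blocked randomization in 1:1 ratio will be used to allocate patients to the two groups". No stratification factor is stated.
- **Visits (Data collection and management).** "Data will be collected at baseline, and at week 16, 26 and 52". The article does not say whether baseline WOMAC pain is one of the repeated outcomes or a covariate.
- **Structural rationale.** The Background lists cartilage growth among the hypothesized mechanisms. On the age criterion, Eligibility says "we set the upper age limit to ensure adequate potential for cartilage regeneration".

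**The concern.** The article names its covariates, so this is a stated choice and not a detail left to an unseen analysis plan. One of the two chosen covariates, the comorbidity count, describes the patient in general. The radiographic grade of the knee under study enters neither the allocation nor the model, although the article treats the structural state of the joint as relevant to how the treatment might work.

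In a trial of this size a visible imbalance in grade can arise by chance. If the grade predicts pain, a pre-specified adjustment would absorb that imbalance and reduce residual variance. It would also settle whether to adjust before anyone has seen the baseline table. What is at stake is a modest amount of precision and the ease of interpreting an imbalanced result. The validity of the primary test is not at stake.

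**Working it through.** **Inputs from the article (Sample size Calculation).** 34 per arm, d = 0.70, 80% power, alpha 0.05, 10% dropout, total 76 (38 per arm). Changes are "25.2 (20.3) points for DPT [32], and 9.53 (26.6) points for NS [51"], with an assumed SD of 26.6. **Assumption, not in the article:** R2, the extra share of outcome variance that the grade explains given the other covariates, taken as 0 to 0.10.

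**1. The plan's own figure.** A two-sided two-sample t-test at d = 0.70 needs 33.02 per arm, rounded up to 34. Power at 34 is 81.2%. 68/0.9 = 75.6, rounded up to 76. The stated size follows from d = 0.70 and takes no credit for any covariate. Separately, the stated inputs give (25.2 - 9.53)/26.6 = 15.67/26.6 = 0.589 rather than 0.70. That is a different point, so both values are carried below.

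**2. How large an imbalance is likely.** Suppose half the participants have the higher grade (assumed). The SD of the between-arm difference in that share is sqrt(2 x 0.5 x 0.5/38) = 0.115. By the normal approximation, P(difference above 15 points) = 0.19 and P(above 20 points) = 0.08, in either direction.

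**3. What that does to the estimate.** For a 50:50 covariate (SD 0.5), a 15-point imbalance shifts the estimate by (0.15/0.5) x sqrt(R2) outcome SDs. This is 0.3 x sqrt(0.03) = 0.05 to 0.3 x sqrt(0.10) = 0.09. The standard error with 34 per arm is sqrt(2/34) = 0.24 SD, so the shift is about 0.2 to 0.4 of one standard error.

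**4. Gain at a single time point.** SE ratio = sqrt(1 - R2); equivalent extra patients = 76/(1 - R2) - 76; power uses d/sqrt(1 - R2) with 34 per arm.

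| R2 (assumed) | SE ratio | Equivalent extra patients | Power, d = 0.70 | Power, d = 0.589 |
|---|---|---|---|---|
| 0 | 1.000 | 0 | 81.2% | 66.8% |
| 0.03 | 0.985 | 2.4 | 82.3% | 68.1% |
| 0.10 | 0.949 | 8.4 | 85.0% | 71.3% |

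**5. Whether the gain reaches the planned contrast.** Step 4 describes one comparison at one time, whereas the plan is a repeated-measures model. There are two cases.

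- *Baseline is one of four repeated outcomes.* A grade main effect subtracts the same amount from the arm difference at every visit. The change in that difference from baseline to week 52 is therefore untouched. Simulation (34 per arm, four visits, autoregressive covariance treated as known, complete data) confirmed this: the largest difference in the estimate was 4e-16. Only grade-by-time can act. With a slope of 0.3 SD on follow-up only, it lowered the SD of the week-52 contrast from 0.331 to 0.324 (correlation 0.5) and from 0.287 to 0.276 (correlation 0.7), about 2-4%. Where the grade acted equally at all visits there was no gain, and the SD rose slightly (0.327 to 0.331).
- *Baseline is a covariate and the follow-up visits are the outcomes.* A grade main effect does act. In simulation the SD of the week-52 estimate fell from 0.248 to 0.238, that is by 0.010/0.248 = 4%.

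**The case against.** The strongest reply is that choosing covariates is a design judgement. The article pre-specifies a model, nothing in it requires adjustment for the grade, and the sample size rests on an unadjusted test. That stands, and it is why this is a suggestion and not a correction.

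A reader might also infer more than the article supports:

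- **That the effect estimate is biased.** It is not. Under randomization, omitting a baseline covariate leaves the estimate unbiased, and the standard error and type I error already allow for chance imbalance. What remains is precision and interpretation conditional on the imbalance seen.
- **That precision is definitely lost.** The article gives no association between grade and WOMAC pain. Its structural rationale concerns how dextrose might work, which points at most to a modified treatment effect and not to prognosis. The Background also describes pain in knee osteoarthritis as multifactorial.
- **That the only severity measure has been ignored.** WOMAC, VAS pain and the performance tests are also measured at baseline. The grade is the only radiographic measure named.
- **That any added term would help.** Step 5 of the working shows otherwise. The same limit applies to the two covariates already listed: entered as main effects with baseline in the outcome vector, they leave the group-by-time contrast unchanged with complete data.

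What survives is that the value is already collected, adjusting for it costs almost nothing, and the trial is small.

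**Conclusion.** The point holds as an optional, low-priority improvement. The article is neither wrong nor contradictory here. The size of the benefit depends wholly on an R2 that it does not supply: a standard error about 1.5-5% smaller at 3-10%, and nothing at zero. The simulated gains of about 2-4% belong to settings where the grade was made prognostic for follow-up pain, so they show that the mechanism works and do not predict its size. The gain also requires a model form in which the grade can act on the treatment contrast.

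**What to change.** In Data analysis, before unblinding, add Kellgren-Lawrence grade as one pre-specified term (ordinal, or lower versus higher grade) to the WOMAC pain model, beside pain duration and comorbidity count. State the form: baseline WOMAC pain as a covariate, with weeks 16, 26 and 52 as the outcomes. If baseline is instead kept in the outcome vector, enter grade-by-time.

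The cost is a sentence of text and one degree of freedom, or three more for grade-by-time, with a negligible loss of precision if the grade turns out not to be prognostic. Randomization, data collection and sample size stay as they are.
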